### Outcome measures

Screening variables: *Depressive symptoms* will be measured using the GDS [13], which has been adapted and validated for the Spanish geriatric population [14]. The shortened, GDS-5 will be used to screen potential participants [15]. The GDS-15 version will be used for the follow-up assessments [16]. *Cognitive function* will be evaluated using the 11-item MMSE, which will be used to screen probable cognitively-impaired individuals (MMSE values below 24 points) [17]. *Sociodemographic information* will be collected on age, gender, marital status, living arrangements, education level, last occupation, and residential neighborhood. Individual socioeconomic status will be obtained through the last occupation of the individual according to the last classification of the Spanish Society of Epidemiology [18]. The residential neighborhood will allow an ecological socioeconomic score to be obtained, based on indicators such as graduate rates, unemployment rates, vehicles, second-hand home prices, and the Disposable Household Income Index [19].

### Main outcomes

*Self-perceived memory* will be measured using a subjective self-reported memory score (from 0 to 10), as well as with the Memory Failures in Everyday life questionnaire (MFE). This questionnaire consists of 28 items and uses a Likert-type scale referring to perception of everyday memory problems [20–22].

*Everyday memory* will be measured using the Rivermead Behavioural Memory Test-3 (RBMT-3) [23]. This cognitive test evaluates different types of memory, such as associative memory, prospective memory, visual memory, topographical memory, and verbal memory. The test provides a General Memory Index and different subtest scales.

*Executive control abilities will be measured in terms of* visual-perceptual ability, working memory and task-switching ability with the Trail Making Test (TMT) [24]. This neuropsychological test is divided into two parts and the score on each part represents the amount of time required to complete the task [25]. Working memory will also be assessed using the digit span scale of the Wechsler Adult Intelligence Scale III (WAIS III).

### Secondary outcomes

*Health-Related Quality of Life* (HRQoL) will be assessed using the Short Form-36 (SF-36) [26, 27], with a validated Spanish version [28, 29]. Of the 36 items, 35 make up eight scales: physical functioning, role limitations due to physical functioning, bodily pain, general health perceptions, vitality, social functioning, role limitations due to emotional problems, and mental health [26].

*Functionality and disability* will be measured with the Spanish Version of the Short-Form Late-Life Function and Disability Instrument (SFLLFDI) [30, 31]. The LLFDI was developed as a comprehensive assessment of function and disability for use in community-dwelling older adults. It contains items that represent functional limitations (inability to perform discreet physical tasks encountered in daily routines) and disability (inability to take part in major life tasks and social roles).

### Intervention-related variables

Other variables related to the implementation of the intervention will be collected, such as the number of sessions the person has attended, the participants’ satisfaction with the workshops, the usefulness of the program, and overall impressions. The professionals conducting the workshops will also evaluate individual and group progress.

### Sample size calculation

The sample size was calculated to detect a difference in everyday memory higher than 2 points (0.5 SD) on the mean RBMT-3 score between the control and the intervention group [32]. Accepting an alpha risk of 0.05 and a beta risk of 0.1 in a bilateral contrast, and assuming a mean score of 16.07 and an SD of 4.19 [33] on the RBMT-3 in the Spanish population aged between 70 and 75 years, 75 individuals in each group will be needed. To ensure this sample size and considering an estimated rate of losses of 20 % in the EG and 40 % in the CG, the final sample size needed is 195 individuals (90 in EG and 105 people in CG, respectively).

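### 75 per group gives about 83% power for 2 points with a two-sided 5% test, not the stated 90%; it matches a one-sided calculation

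*Protocol article*

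**What the plan says.** The Sample size calculation section of the protocol article gives every input for a comparison of two means. The aim is to "detect a difference in everyday memory higher than 2 points (0.5 SD) on the mean RBMT-3 score" between control and intervention groups. The error rates are set by "Accepting an alpha risk of 0.05 and a beta risk of 0.1 in a bilateral contrast", that is, a two-sided 5% test with 90% power. The variability comes from Spanish population data, "assuming a mean score of 16.07 and an SD of 4.19". The section concludes that "75 individuals in each group will be needed". It then adds an allowance for an "estimated rate of losses of 20 % in the EG and 40 % in the CG" to reach 90 and 105 enrolled, 195 in total.

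The section mentions no baseline correlation, covariate adjustment, repeated measurement or other device that would reduce the variance below the SD of 4.19. It is the only power statement in the article, and RBMT-3 is the only outcome it covers.

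**The concern.** A standardised difference of just under half an SD, tested two-sided at 5% with 90% power, normally needs more than 75 per group. A figure that low suggests that one of the stated conditions was not used in the calculation.

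The stated power tells readers how to weigh a negative result. The article's Implications section says the findings should inform decisions on public spending for such workshops. If the chance of missing a true 2-point benefit is about one in six rather than one in ten, a null result would be read with more confidence than the design supports.

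**Working it through.** **Inputs**, all from the Sample size calculation section:
- difference d = 2 points, also labelled 0.5 SD. The two differ slightly: 2/4.19 = 0.477 SD, and 0.5 × 4.19 = 2.095 points. Both readings are checked.
- SD = 4.19
- alpha = 0.05, two-sided
- power = 0.90
- equal evaluable groups

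**Formula**, per group: n = 2 × (z_alpha + z_beta)² × (SD/d)², with z_beta = 1.2816 for 90% power. For d = 2, (SD/d)² = 2.095² = 4.389. For d = 0.5 SD, (SD/d)² = 4.

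**Reproducing the stated 75.** With the stated two-sided test, z_alpha = 1.960:
- d = 2: 2 × (1.960 + 1.2816)² × 4.389 = 2 × 10.508 × 4.389 = 92.2, so 93 (exact t test: 93.2, so 94).
- d = 0.5 SD: 2 × 10.508 × 4 = 84.1, so 85 (exact t test: 86).

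Neither is 75. With a one-sided test, z_alpha = 1.645:
- d = 2: 2 × (1.645 + 1.2816)² × 4.389 = 75.2.
- d = 0.5 SD: 68.5, so 69.

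Of these four readings, only the one-sided test for 2 points lands on 75. Strict rounding up would make it 76.

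**Power that 75 per group provides.** The standard error of the difference is 4.19 × √(2/75) = 0.684.

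| Target | Target/SE | Minus 1.960 | Power, normal | Power, exact t |
|---|---|---|---|---|
| 2 points | 2.923 | 0.963 | 83.2% | 82.7% |
| 0.5 SD (2.095 points) | 3.062 | 1.102 | 86.5% | 86.0% |

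One-sided power at 75 per group for 2 points is 89.9% by the normal formula, which again matches the stated 90%.

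**Difference detectable with 90% two-sided power at 75 per group.** (1.960 + 1.2816) × 0.684 = 2.22 points by the normal formula, or 2.23 with the t distribution.

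**Size of the gap.** For 2 points, the stated number is 93 − 75 = 18 short per group (19 with the exact t test). For 0.5 SD it is 10 to 11 short. Rounding does not explain either gap. The type II error is 17.3% for 2 points and 14.0% for 0.5 SD, that is, 1.7 and 1.4 times the stated 10%.

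**The case against.** The strongest objection is that the main analysis is not a two-sample t test at one visit. The Statistical analysis section plans a repeated-measures mixed model with baseline, two follow-ups and a group-by-time interaction, and such a model can use the baseline score to reduce variance. Using the normal formula and assumed correlations:
- Adjusting for baseline multiplies n by (1 − r²). From 92.2, 75 per group is enough once the baseline correlation r is about 0.44.
- A change-score analysis multiplies n by 2(1 − r) and reaches 75 at r of about 0.6. At r = 0.4 its two-sided power at 75 per group is lower, about 76%.

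The power of the planned model could therefore lie above or below 83%, and the check above does not settle it. What it settles is that the stated calculation is wrong on its own terms. The section compares means using a cross-sectional SD and states no correlation, so it cannot borrow a gain it never claims.

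It is also fair to say that the one-sided origin is an inference from a close numerical match; the article does not say how 75 was obtained. The defect does not depend on it, because 75 is wrong for the stated two-sided test whatever its source.

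Finally, the error biases no estimate and leaves the type I error intact. The plan reports 95% confidence intervals, which help in reading a null result. That limits the harm but does not make the stated power correct.

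**Conclusion.** The concern holds. With the section's own inputs, 90% power needs 93 to 94 evaluable per group for 2 points, or 85 to 86 for 0.5 SD. With 75 per group, two-sided power is 82.7% or 86.0% respectively. These figures assume a two-sample t test, SD 4.19, equal groups and independent observations, before losses and before any clustering within workshop groups.

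The enrolment figures do not restore 90%:
- 90 and 105 enrolled, at the stated 20% and 40% losses, leave 72 and 63 evaluable, with about 78% power for 2 points.
- The Abstract gives a total of 230. Split equally (an assumption), 115 per arm at the same losses leaves 92 and 69, with about 85% power.

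The loss allowance and the discrepancy between 195 and 230 are separate points; they matter here only because neither rescues the claim.

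**What to change.** Correct the Sample size calculation section so that the power, the sidedness and the number agree. It should state that, for a two-sided 5% comparison with SD 4.19:
- 75 evaluable participants per group give about 83% power for a 2-point difference, or 90% power for 2.23 points;
- 93 to 94 evaluable per group would be needed for 90% power at 2 points.

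Choose either 2 points or 0.5 SD as the target and use it throughout. For 0.5 SD, the figures are 86% power at 75 per group and 85 to 86 per group for 90%. Once the enrolment total and loss allowance are reconciled, give the power for the evaluable numbers actually expected as well.

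If the sponsor wishes to rely on baseline adjustment to recover power, the section should state the assumed correlation, its source and the resulting power.

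The cost is a rewording of one paragraph and a less favourable stated power. This correction does not require a change in enrolment.

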**Methods/design:**

A randomized controlled trial will be performed in health care centers in Barcelona (Spain) through comparison of a group of individuals participating in memory training workshops (experimental group) with another group with similar characteristics not participating in the workshops (control group). The intervention will consist of twelve 90-minute group sessions imparted once a week by a psychologist specialized in memory training. The groups will each comprise approximately 15 people, for a total number of 230 patients involved in the study. Each session has its own objectives, materials and activities. The content of the intervention is based on memory training from different perspectives, including cognitive and emotional aspects and social and individual skills. Data will be collected at baseline, at 3–4 months and at 6 months. To assess the efficacy of the intervention on cognitive function, health-related quality of life and functionality, a statistical analysis will be performed by fitting a repeated-measures mixed effects model for each main outcome: *Self-perceived memory,* measured by a Subjective Self-reported Memory Score (from 0 to 10) and by the Memory Failures in Everyday life questionnaire (MFE); *Everyday memory,* measured using the Rivermead Behavioural Memory Test-3 (RBMT-3) and *Executive control abilities,* measured in terms of visual-perceptual ability, working memory and task-switching ability with the Trail Making Test (TMT) and with the digit span scale of the Wechsler Adult Intelligence Scale III (WAIS III).

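### The loss allowance in the sample size section is n × (1 + loss), so 195 leaves 72 and 63 evaluable rather than 75 per arm; the abstract's total of 230 is unreconciled, and the 90 % power claim fails either way

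*Protocol article*

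**What the plan says.** All of this is in the protocol article.

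- **Target difference** (Sample size calculation): "a difference in everyday memory higher than 2 points (0.5 SD) on the mean RBMT-3 score", "assuming a mean score of 16.07 and an SD of 4.19".
- **Error rates** (same section): "Accepting an alpha risk of 0.05 and a beta risk of 0.1 in a bilateral contrast", which means a two-sided test at 5 % with 90 % power.
- **Evaluable number** (same section): "75 individuals in each group will be needed".
- **Allowance for losses** (same section): it is introduced by "To ensure this sample size and considering an estimated rate of losses", with the rates given as "considering an estimated rate of losses of 20 % in the EG and 40 % in the CG". The result is that "the final sample size needed is 195 individuals (90 in EG and 105 people in CG, respectively".
- **Total in the abstract** (Methods/design): "for a total number of 230 patients involved in the study". The article does not derive this figure, split it by arm or relate it to 195.

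**The concern.** A loss rate applies to the people enrolled, so enrolment must be divided by the retained fraction. The stated numbers come instead from multiplying the required number by one plus the loss rate. The two rules are close when losses are small, but they differ markedly at 40 %. The section says that its purpose is to secure 75 per arm, and on its own inputs it does not.

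The power of the everyday-memory (RBMT-3) comparison is at stake, and so is the reading of a null result. A reader told that the trial had 90 % power for 2 points would take a null finding as stronger evidence against that effect than the design supports. The abstract's 230 adds uncertainty about which total the power statement belongs to.

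**Working it through.** **Inputs, all from the Sample size calculation section unless noted:** two-sided alpha 0.05; power 0.90; difference 2 points, also called 0.5 SD; SD 4.19; 75 evaluable per arm; losses 20 % (EG) and 40 % (CG); enrolment 90 + 105 = 195. The abstract gives 230.

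The two statements of the effect differ slightly: 2/4.19 = 0.477 SD, while 0.5 × 4.19 = 2.095 points. Both are carried through.

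**1. Reproducing the plan's figure, n × (1 + loss)**
- EG: 75 × 1.20 = 90
- CG: 75 × 1.40 = 105
- Total: 195, an exact match

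**2. What 195 leaves at the stated losses, enrolled × (1 − loss)**
- EG: 90 × 0.80 = 72
- CG: 105 × 0.60 = 63
- Total: 135, against the 150 required

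Ending with 75 in each arm would need losses of only 1 − 75/90 = 16.7 % and 1 − 75/105 = 28.6 %.

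**3. Enrolment that does keep 75 per arm, n/(1 − loss)**
- EG: 75/0.80 = 93.75, so 94
- CG: 75/0.60 = 125
- Total: 219, which is 24 more than 195 (4 in EG, 20 in CG)

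The abstract's 230 equals neither 195 nor 219.

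**4. Power.** This is a two-sided t-test at 0.05. The noncentrality is δ / (SD × √(1/n₁ + 1/n₂)); for 72 and 63 at 2 points it is 2 / (4.19 × 0.1725) = 2.77.

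| Evaluable EG / CG | 2 points, SD 4.19 | 0.5 SD |
|---|---|---|
| 75 / 75 | 82.7 % | 86.0 % |
| 72 / 63 | 78.4 % | 82.1 % |

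The difference detectable with 90 % power is 2.36 points at 72/63, and already 2.23 points at 75/75.

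**5. Splitting the shortfall from 90 %**
- For 2 points, the loss arithmetic costs 82.7 − 78.4 = 4.3 percentage points. The other 90 − 82.7 = 7.3 come from the base number.
- For 0.5 SD, the corresponding figures are 86.0 − 82.1 = 3.9 and 90 − 86.0 = 4.0.

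The base number of 75 does not follow from the stated inputs. Two-sided, 90 % power needs 93 per arm for 2 points or 85 for 0.5 SD. A one-sided test for 2 points needs 76, which is close to 75, but the section specifies a two-sided test.

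**6. If 230 is the target.** The article gives no split, so two are assumed.
- 115/115: 115 × 0.80 = 92 and 115 × 0.60 = 69; power 84.6 % for 2 points
- About 106/124 (the 90:105 ratio): 106 × 0.80 ≈ 85 and 124 × 0.60 ≈ 74; power 84.7 % for 2 points

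**The case against.** **230 may be the planned enrolment, above a calculated minimum.** The abstract speaks of people involved and the sample size section of people needed, and 230 exceeds both 195 and 219. This is possible, and if so the 72/63 shortfall does not arise in that form. But the safety of 230 depends on a split the article does not give: at 1:1 the control arm keeps 69, and at the 90:105 ratio 74. A split near 94:125 would keep 75 in each. The sample size section's own arithmetic stays wrong in every case.

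A reader might also infer from the two totals that staff cannot tell when recruitment is complete. The article does not support that. It is a condensed account, and nothing in it shows that recruitment is run from its abstract. What stands is that the two figures are not reconciled.

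**The planned analysis is stronger than a t-test on completers.** The Statistical analysis section specifies a repeated-measures mixed model that includes baseline and is fitted to all available data. This could recover some power. The article gives no correlation between baseline and follow-up, so the gain cannot be established. As an assumption only, scaling the residual SD by √(1 − r²) gives, for 72/63 and 2 points, about 82 % at r = 0.3, 89 % at r = 0.5 and 93 % at r = 0.6. So 78 % is probably a low figure for the planned model. This does not rescue the section, which sizes the trial on a two-group comparison of means with 75 retained per arm and fails on those terms.

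**Conclusion.** The point holds. The loss allowance is wrong as written: 195 yields 72 and 63 at the plan's own losses, not 75 and 75, and the abstract's 230 is left unexplained. Power at 72/63 is about 78 % for 2 points (82 % for 0.5 SD). This rests on the stated SD and losses and on an unadjusted two-sided t-test.

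Two stronger readings are tempting and should be avoided. One is that the whole fall from 90 % to 78 % is due to the loss arithmetic. It accounts for only about 4 percentage points; the rest comes from a base of 75 that is too small for the stated two-sided test. The other is that correcting the inflation to 219 restores the design. It restores 75 per arm, but with only about 83 % to 86 % power.

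**What to change.** 1. State one enrolment total, with its split per arm, identically in the abstract and in the sample size section.
2. Replace the n × (1 + loss) step with the evaluable numbers that this total yields under losses of 20 % and 40 %.
3. Restate the power for those numbers and drop the 90 % claim:
   - if 195 stands, about 72 + 63 evaluable and 78 % for 2 points (82 % for 0.5 SD);
   - if 230 is the target, about 85 % for 2 points with a split of 115/115 or about 106/124; recompute for any other split.
4. If the team wants credit for the baseline-adjusted mixed model, state the assumed correlation and its source.

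The cost is rewording in two places and a less favourable power figure, with no extra participants. Raising enrolment from 195 to 219 is a separate decision: it would mean 24 more people and would still not justify the 90 % claim.

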### Statistical analysis

Baseline comparability between the study arms will be assessed through bivariate analyses of the pre-test data set group (dependent and independent variables) comparing the control and the experimental arms. The chi-square test will be used to compare qualitative data, as well as the Student *t* test or the Mann–Whitney test for quantitative data, depending on the normality of the distribution. If differences are found in baseline characteristics, we will consider adjusting for these variables in the efficacy analysis.

A descriptive analysis will be conducted for results at baseline, at the immediate follow-up and at the delayed follow-up for the EG and CG. Categorical outcomes will be described through raw frequencies or percentages, and continuous outcomes will be described through mean scores and standard deviations. Effect measures for each outcome at the immediate and delayed follow-ups will be computed as the mean of the differences of the aggregated scores for the EG and CG. Effect measures will be presented with their 95 % confidence intervals.

The main statistical analyses to assess the efficacy of the intervention on self-perceived memory, everyday memory and executive control abilities will be performed using a repeated-measures mixed effects model for each main outcome defined in the protocol [34]. In each model, the independent variables will be the group (EG or CG), time (baseline, immediate follow-up or delayed follow-up) and any relevant characteristics that differ between the groups at the baseline assessment (e.g., age or educational level). An interaction term between time and group will be included in the analyses. The models will be fitted with the available data, ignoring missing data.

To determine whether the results have been influenced by missing data, we will conduct sensitivity analyses by fitting the models with completed datasets obtained by imputing the missing data [35]. In this analysis, missing values for the immediate or delayed post-test assessments will be imputed through the Last Observation Carried Forward (LOCF) strategy. According to this strategy, missing values will receive the value obtained by the participant in the previous assessment. In addition, we will perform sensitivity analyses restricted to those participants attending at least 80 % of the sessions.

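### The reported effects and 95% CIs are defined outside the mixed model that tests efficacy, and can be biased and disagree with it if the expected losses are related to baseline score

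*Protocol article*

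**What the plan says.** All of this is in the Statistical analysis section of the protocol article, except the loss rates.

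- **Descriptive paragraph.** It opens: "A descriptive analysis will be conducted for results at baseline, at the immediate follow-up and at the delayed follow-up for the EG and CG". After the summaries of categorical and continuous outcomes, it defines the effect that compares the two arms: "Effect measures for each outcome at the immediate and delayed follow-ups will be computed as the mean of the differences of the aggregated scores". It then adds: "Effect measures will be presented with their 95 % confidence intervals".
- **Efficacy paragraph.** The main efficacy analysis "will be performed using a repeated-measures mixed effects model for each main outcome defined in the protocol". Group, time and any characteristics that differ at baseline are the independent variables, and "An interaction term between time and group will be included in the analyses". On missing data: "The models will be fitted with the available data, ignoring missing data". The paragraph does not say which estimate or interval is to be reported from the model.
- **Sensitivity paragraph.** LOCF imputation is planned for refits of the models. It is not mentioned for the effect measures.
- **Sample size calculation.** The enrolled numbers were set "considering an estimated rate of losses of" 20% in the EG and 40% in the CG.

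**The concern.** Two analyses sit side by side. One supplies the effect sizes and intervals, the other the efficacy test. The only effect measure that the article defines is a difference in aggregate scores. Since covariates and imputation are attached only to the models, that difference is most naturally an unadjusted one among participants who have a score at the visit in question.

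The two analyses handle loss differently. The available-data mixed model also uses the baseline scores of people who later leave, and it needs only missing at random. The raw difference does not use those scores. When loss depends on baseline score and the arms lose people at different rates, the remaining participants are no longer comparable between arms.

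The definition also leaves open whether follow-up scores or changes from baseline are compared. The two readings err in opposite directions under the same loss mechanism, so the choice matters and should not be made after the data are seen. At stake are the size and interval that readers will take away, in a trial whose Implications section wants its findings considered when public resources are allocated.

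**Working it through.** **Inputs from the article (Sample size calculation).** RBMT-3 mean 16.07, SD 4.19; target difference 2 points; 90 EG and 105 CG enrolled; losses 20% and 40%. This leaves 90 × 0.8 = 72 and 105 × 0.6 = 63. The plan gives no figure for the effect measure itself, so there is none to reproduce.

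**Assumptions, not in the article.** True effect 2 points at follow-up; correlation r between baseline and follow-up of 0.5 or 0.7; loss logistic in baseline score, with log-odds −0.5 or −1 per SD (low scorers leave more often), either in both arms or in the CG only.

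**Formulas.** Let D be the mean baseline score of the EG participants who remain, minus that of the CG participants who remain. If loss depends on baseline only:

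- difference in follow-up means = 2 + r × D
- difference in mean change = 2 − (1 − r) × D
- model group-by-time contrast = 2, because it corrects for the baseline shift

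**Example.** With log-odds −1 in both arms, the remaining EG participants average 0.726 points above the full-arm baseline mean and the remaining CG participants 1.392 above, so D = 0.726 − 1.392 = −0.666. At r = 0.7 the follow-up difference is 2 − 0.7 × 0.666 = 1.53 and the change difference is 2 + 0.3 × 0.666 = 2.20.

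| Loss related to baseline | D | Follow-up difference, r = 0.5 / 0.7 | Change difference, r = 0.5 / 0.7 |
|---|---|---|---|
| Not at all | 0 | 2.00 / 2.00 | 2.00 / 2.00 |
| Both arms, −0.5 | −0.390 | 1.81 / 1.73 | 2.20 / 2.12 |
| Both arms, −1 | −0.666 | 1.67 / 1.53 | 2.33 / 2.20 |
| CG only, −0.5 | −0.793 | 1.60 / 1.44 | 2.40 / 2.24 |
| CG only, −1 | −1.392 | 1.30 / 1.03 | 2.70 / 2.42 |

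A simulation with 1,000,000 participants per arm gives the same picture: 1.02 to 1.81 for follow-up means and 2.11 to 2.69 for change when loss is related to baseline, and 1.99 to 2.01 for the model contrast in all scenarios.

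**Check under a different mechanism.** If loss depends instead on the unobserved follow-up score (log-odds −1 per SD, both arms), the model contrast averages about 1.5 (r = 0.5) and 1.6 (r = 0.7), the change difference about 1.7 and 1.8, and the follow-up difference about 1.3. Missing at random fails here, and all three are biased.

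**Precision, loss unrelated to score.** Let c = 1/72 + 1/63 = 0.02976 and n = 1/90 + 1/105 = 0.02063.

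- SE of follow-up difference = 4.19 × √c = 0.72
- SE of change difference = 4.19 × √(2(1 − r)c): 0.72 at r = 0.5, 0.56 at r = 0.7
- SE of model contrast = 4.19 × √((1 − r²)c + (1 − r)²n): 0.81 at r = 0.3, 0.69 at r = 0.5, 0.55 at r = 0.7

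**The case against.** The strongest reply is that the sentence is descriptive by its position and that the next paragraph already gives inference to the mixed model. Interaction contrasts with intervals are routine output, and a condensed article need not list them. This stands in part: the efficacy test is not at risk, and nothing says that model contrasts will be withheld. It does not remove the point, because the article does state a definition of the effect and attaches an interval to it, and that definition is not the model's.

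It is also fair that the restriction to participants with data is inferred, not stated. It follows from where imputation and covariates are mentioned, and is the natural reading, not a certain one.

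A reader might infer more than the article supports:

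- *Unequal losses alone bias the raw difference.* They do not. With loss unrelated to score, D = 0 and the estimates agree on average. The article gives loss rates but no link to score.
- *The raw difference is valid only if loss is unrelated to every score.* This is too strict. A change difference needs loss unrelated to change, and loss that shifts both arms' baseline means equally cancels.
- *The model contrast is always more precise.* It is not. At r = 0.3 its SE is 0.81 against 0.72 for the follow-up difference, and at r = 0.7 the change difference nearly matches it (0.56 against 0.55). The article gives no correlation.
- *The model contrast is correct whatever the losses.* It is protected under missing at random. Where loss depends on the follow-up score it is biased too, and in the check above the change difference lies closer to the truth.

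**Conclusion.** The point holds as one about the reported estimate and interval, not the main test. The article defines its effect measures and 95% CIs apart from the model that judges efficacy, leaves follow-up and change scores undistinguished, and expects losses of 20% and 40%. If low scorers leave more often, the reported effect can be too small (follow-up means) or too large (change scores), and can disagree with the model.

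On a true effect of 2 points, the illustrations give errors of about −0.2 to −1.0 point for follow-up means and +0.1 to +0.7 point for change scores. These sizes rest on the assumed baseline-dependent loss and on correlations of 0.5 to 0.7. They are not forecasts for this trial, and the error is zero on average if loss is unrelated to score. The case for the model contrast is that it matches the planned test and needs only missing at random.

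**What to change.** Replace the definition with wording such as: the effect at the immediate and at the delayed follow-up is the group-by-time contrast at that visit (the difference between arms in change from baseline) from the repeated-measures mixed model, with its 95% confidence interval. Keep raw means, SDs and raw differences, labelled as descriptive only, and say whether a raw difference refers to follow-up or change scores.

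For the main outcomes this costs a sentence or two. It needs no new data and no new analysis, since the model is already planned. The article names the model only for the main outcomes, whereas the effect measures cover each outcome, so using the same definition for the secondary outcomes would mean fitting the same model to them.
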